### 8. Statistical analysis

The primary statistical analysis will be to estimate the association of match‐paired binary responses (molecular and radiological progressors) since the results of the two tests are not independent. For McNemar’s test of paired proportions using the Miettinen normal approximation with a two‐sided significance level of 0.05, a sample size of 60 achieves a power of at least 0.8 when the discordant proportions are 0.05 (5%) and 0.25 (25%) of the total number. The ratio of progressors will inform the precision of the IC for the molecular analysis. Study results will be shared in peer reviewed journal articles.

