**Methods:**

RECONCILE is an ethics approved (20/LO/0366) single centre, prospective, longitudinal, observational cohort study of recently diagnosed (within 12 months), organ-confined Gleason 3 + 4 cancers (MCCL ≤10mm) currently under active surveillance. 60 treatment-naïve participants with a concordant MRI lesion (Likert score 4 or 5) and PSA ≤ 15 ng/ml will be recruited.

Blood, urine and targeted prostate tissue cores will be subject to next generation sequencing at baseline and one year in all participants. Semen will be collected from a specified sub-population. Baseline and interval MR images will be extracted from standard of care prostate MRI ahead of radiomic analysis. Data extracted from radiological and biological samples will be used to derive the association of molecular change and radiological progression, the primary outcome of the study.

To compensate for spatial intratumoral heterogeneity and inherent sampling bias, a molecular index will be derived for each participant using the molecular profile of tumour tissue at both baseline (MolBL) and one year (MolFU). We will extract a ΔMolBL:MolFU score for each participant. Molecular progression will be defined as a MolBL:MolFU score >95% CI of the combined ΔMolBL scores. Radiological progression is defined as a PRECISE score of 4 or 5. The study is powered to detect an association with a statistical power of 80%.

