### 3.1 Primary objective

The primary objective is to estimate the association of molecular changes with radiological progression events of small, localised Gleason 3 + 4 tumours visible on mpMRI.

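### The 80% power is for McNemar's test, which compares the two progression rates; it does not support the claim of power to detect an association between molecular and radiological progression.

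*Protocol article*

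**What the plan says.** The primary objective (section 3.1, and in similar terms section 1.2) is to "estimate the association of molecular changes with radiological progression events". The primary outcome (section 7.1) is the proportion of pairs in which the molecular and radiological classifications are concordant. Section 4.3 plans a 2×2 table of radiological progression (R+/R−) by molecular change (M+/M−) to study how the two relate.

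Section 8 opens in the same spirit: the main analysis is meant to measure how the two paired yes/no classifications are associated, on the ground that they depend on each other. The only test it then names is McNemar's "test of paired proportions using the Miettinen normal approximation", two-sided at 0.05. Its sample-size statement is that "a sample size of 60 achieves a power of at least 0.8 when the discordant proportions are 0.05 (5%) and 0.25 (25"%). The abstract (Methods) turns this into "The study is powered to detect an association with a statistical power of 80"%.

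The document gives no odds ratio, phi, kappa, expected concordance or expected progression rate, and does not say which discordant cell is the 25% one.

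**The concern.** McNemar's null hypothesis is that the two discordant cells are equal, which is the same as P(M+) = P(R+). How the concordant pairs divide between both-positive and both-negative never enters the test, yet association and chance-corrected agreement depend on that division. The planning alternative of 5% against 25% describes two progression rates 20 percentage points apart. It says nothing about whether the same patients progress on both measures.

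The stated reason for the test, that the two results are not independent, does not help. Dependence between M and R is the question under study. Pairing justifies McNemar's test for comparing two paired rates and does not make it a test of association.

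At stake are the only stated basis for n = 60 and the meaning of the primary result. The calculation would be satisfied by two unrelated classifications with different rates, and could fail for two closely linked ones with similar rates.

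**Working it through.** **Inputs.** From section 8: n = 60 pairs, two-sided α = 0.05, discordant proportions 0.25 and 0.05. Hence ψ = 0.25 + 0.05 = 0.30, d = 0.25 − 0.05 = 0.20, and concordant pairs 1 − 0.30 = 0.70. Section 2.1 sets 60 as the evaluable number and section 4.8 replaces non-evaluable cases, so no allowance for dropout is applied.

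**1. The plan's own figure.** Miettinen power = Φ{[d√(nψ) − 1.96ψ] / √(ψ² − d²(3 + ψ)/4)}.
- Numerator: 0.20 × √18 − 1.96 × 0.30 = 0.8485 − 0.5880 = 0.2605.
- Denominator: √(0.09 − 0.033) = 0.2387.
- Power = Φ(1.091) = 0.862.
- For 80% power, n = (0.5880 + 0.8416 × 0.2387)² / (0.30 × 0.04) = 51.9, so 52.

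By full enumeration at n = 60, the asymptotic McNemar test has power 0.857 and the exact test 0.797. The statement in section 8 is therefore sound as McNemar power under the approximation it names.

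**2. Same discordances, no association.** Let a be the both-positive proportion. Independence requires a(0.70 − a) = 0.25 × 0.05 = 0.0125, and the smaller root is a = 0.0183. The two rates are then 0.0183 + 0.25 = 26.8% and 0.0183 + 0.05 = 6.8%, and the odds ratio is 1. McNemar's test rejects with probability 0.797 (exact) to 0.857 (asymptotic). Fisher's exact test rejects with probability about 0.02.

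**3. Strong association, equal rates (illustrative assumption).** Both positive 20%, discordances 5% and 5%, both negative 70%. Odds ratio = (0.20 × 0.70)/(0.05 × 0.05) = 56. McNemar's test rejects with probability 0.013 (exact) to 0.048 (asymptotic), and Fisher's test with probability above 0.999. With perfect agreement there are no discordant pairs, so McNemar's test cannot reject.

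**4. Power for association at the stated discordances.** The document does not give the split of the concordant 70%, so each row below is an assumption. Odds ratio = a(0.70 − a)/0.0125. Fisher power is at n = 60, by enumeration of all 2×2 tables.

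| Both positive (assumed) | Odds ratio | Fisher power | McNemar power (exact–asymptotic) |
|---|---|---|---|
| 1.8% | 1.0 | 2% | 80–86% |
| 5% | 2.6 | 17% | 80–86% |
| 10% | 4.8 | 50% | 80–86% |
| 15% | 6.6 | 74% | 80–86% |
| 20% | 8.0 | 87% | 80–86% |
| 35% | 9.8 | 95% | 80–86% |
| 55% | 6.6 | 74% | 80–86% |
| 65% | 2.6 | 17% | 80–86% |

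The McNemar column is constant because the concordant split plays no part in it. The Fisher column rises to a maximum at an even split and falls again. Pearson's chi-square test is somewhat more powerful (about 4% in the first row, 97% at the maximum) and shows the same pattern.

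**5. The stated outcome.** In every row the proportion of concordant pairs is 70%, while kappa runs from 0 (first row) to 0.42 (even split). Raw concordance therefore also needs a chance-corrected companion before it can speak to association.

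**The case against.** The strongest defence is that section 8 calls the primary analysis estimation of an association and names McNemar's test only in the sample-size sentence. Section 4.3 plans the full 2×2 table, concordant cells included, and an analysis plan not shown may name the measure. This has some force: a reader might infer that a significant McNemar result would be reported as an association, and the document does not say so. But the defence leaves the power claim where it was. The abstract states power for an association, and the calculation behind it is for equality of rates. That is a mismatch between two statements on the page, not an omitted detail.

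Three further readings go too far:

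- **That the 80% is shown to be false.** It is not. With the concordant pairs split near the middle, Fisher power exceeds 80%. The claim is unsupported by the calculation given, which is a weaker statement.
- **That 80% power needs a radiological progression rate a little above 20%.** Fisher power reaches 80% at about 17% both positive. If M+R− is the 25% cell, R+ is then 17 + 5 = 22%; if the cells are the other way round, R+ is 17 + 25 = 42%. The document does not say which applies. Power also drops below 80% again beyond about 70 − 17 = 53% both positive, so no single threshold describes it.
- **That McNemar's test must miss every perfect association.** This holds for perfect agreement only. If every R+ is also M+ (cells 20%, 25%, 0%, 55%), the odds ratio is infinite and McNemar's test rejects almost always, because the rates differ. The test is uninformative about association; it is not consistently blind to it.

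**Conclusion.** The point holds as an error in what is written. The objective and the abstract's power claim concern association, and the outcome concerns concordance, while the sole test and power calculation concern equality of two progression rates. The arithmetic in section 8 is correct for McNemar's test, but it does not carry over to the stated question.

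The planned calculation gives 80–86% rejection with no association and 1–5% with an odds ratio of 56 and equal rates. Power for association at n = 60 and the stated discordances lies anywhere from about 2% (no association) to 95% (Fisher) over the splits examined. The discordances, α and n are the document's; the concordant splits, the odds-ratio-56 scenario and the use of Fisher's test as the yardstick are assumptions made here. Exchanging the two discordant cells changes which rate belongs to which measure and leaves the power figures as they are. Because this concerns the primary analysis and the only stated basis for n = 60, it should be corrected before the two classifications are brought together.

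**What to change.** In section 8, name as primary analysis a measure of association or agreement on the 2×2 table, for example Fisher's exact test with the odds ratio or phi and a 95% confidence interval. Report the section 7.1 outcome, the proportion of concordant pairs, with its 95% confidence interval, and kappa as the chance-corrected measure. Keep McNemar's test only as a secondary comparison of the two progression rates.

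Replace the power sentences in section 8 and the abstract with the power, or the expected interval width, of n = 60 for that analysis. Give it over a stated range of progression rates and say, as an assumption, which discordant cell is 25%. As an example of a precision statement, at 70% concordance the normal-approximation half-width is 1.96 × √(0.70 × 0.30/60) = 0.116, about ±12 percentage points. Do not quote a single progression rate as the point at which 80% is reached.

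The cost is wording only, with no new data or participants. The restated power may be less favourable if progressors are few.

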## 9. Ethical considerations

The study abides by the principles of the Declaration of Helsinki and received regulatory approval from the Regional Ethics Committee (London–Stanmore 20/LO/0366, 15 April 2020). RECONCILE is published on clinicaltrials.gov (ClinicalTrials.gov identifier: NCT04340245).

## 10 Discussion and limitations

RECONCILE (NCT04340245) will identify molecular markers associated with radiological progression events in a cohort of localised, newly diagnosed Gleason 3 + 4 tumours. Each tumour will be deeply characterised using MRI-targeted histology within a standard of care pathway. Fluidic (blood, urine, semen) and radiomic markers of change will also be assessed. Markers will be correlated against standard of care MRI-targeted histology and long-term oncological outcomes extracted from national health records. By characterising the first detectable radiological progression events within this cohort, and defining image-based progressor and non-progressor cohorts, we may accelerate baseline risk stratification for a significant proportion of men.

This is particularly relevant to the Gleason 3 + 4 cohort which forms the bulk of incidentally detected prostate cancers [19]. Prospective and retrospective data sets suggest that initial active surveillance is likely to be a satisfactory option for men with localised, low-intermediate grade, prostate tumours [3,20]. This is particularly pertinent since radical treatment, the side-effect profile of which is well documented, remains an option for this cohort in several key clinical guidance [4]. Further stratification of the cohort is necessary to spare premature, or altogether unnecessary, intervention.

mpMRI has redefined localised prostate cancer diagnostics and imaging-led surveillance strategies. Novel tests such as radiomic, tissue-based and fluidic biomarkers may further refine risk stratification at baseline and guide the need for intervention by predicting risk of progression. RECONCILE represents the first efforts to assess this prospectively in a cohort of Gleason 3 + 4 tumours. Numerous molecular aberrations are known to be prognostic for prostate cancer recurrence and differ between early, and advanced disease. Such markers may represent predictors of progression risk at baseline [8]. Novel imaging techniques also show promise in the detection and risk stratification of localised prostate cancers. An integrated approach using clinical, molecular (whether fluidic or tissue-based) and imaging analysis may therefore provide more accurate risk assessment and distinguish “progressors” from tumours less likely to progress and prove to be more accurate than histopathological grade–the current gold standard.

### 10.1 Limitations

The RECONCILE protocol has some potential limitations. First, biomarkers of progression will only be validated against known Gleason 3 + 4 tumours. Further studies would need to assess potential biomarkers of progression against further grade groups in order to develop more clinically useful tests. The imaging and biomarker platform provided by the ReIMAGINE Risk study (NCT04060589) may achieve this in part but does not assess radiological progression events specifically.

Second, the study does not contain a specific control group. Rather, control tissue is collected from an area of Likert / PIRADS score less than or equal to 2 during each research biopsy. This step mitigates against the absence of a normal MRI cohort, accounts for molecular heterogeneity within normal gland tissue and will act as a control. Molecular profiling and long term follow up of localised and advanced prostate cancers undertaken by other groups will provide a comparator for the deeply characterised Gleason 3 + 4 cohort studied within RECONCILE and may add context to our results.

Third, many patients referred for secondary care assessment and therefore captured within the study population are referred because of a raised PSA level. Further work may be required to assess the applicability of findings to a cohort of men with a normal PSA. A small subset of men within RECONCILE will be recruited following participation within the ReIMAGINE Prostate Cancer Screening study [21]. ReIMAGINE Screening has been designed to assess the feasibility of bi-parametric prostate MRI as a screening tool for prostate cancer. Patients may screen positive on the basis of either, or both, MRI positivity and raised PSA density. This cohort may broaden the spectrum of patients recruited to RECONCILE to include some participants with a normal PSA.

## 11. Conclusion

Intermediate risk, localised prostate cancers are amenable to a range of management strategies, including active surveillance, focal ablation, radical prostatectomy and radiotherapy. UK clinical guidance supports the use of active surveillance as a strategy to reduce overtreatment of low-intermediate risk disease.

RECONCILE (NCT04340245) will identify molecular and radiomic markers associated with clinical and radiological progression events in a cohort of localised, newly diagnosed Gleason 3 + 4 tumours which have been deeply characterised with MRI-targeted histology within a standard of care pathway. Markers will be correlated against standard of care MRI-targeted histology and oncological outcomes.

## Abbreviations

eCRF: Electronic Case Report Form
EU: European Union
FFPE: formalin-fixed paraffin-embedded
H&E: haematoxylin and eosin
HTA: Human Tissue Authority
MRI: magnetic resonance imaging
MTA: material transfer agreement
mpMRI: multiparametric magnetic resonance imaging
NHS: National Health Service
PCa: prostate cancer
PSA: prostate specific antigen
REC: Research Ethics Committee
SOP: Standard Operating Procedure
TRUS: Transrectal Ultrasound
UCL: University College London
